#### 2.2.1 Primary endpoint

The central parameter of the study is the performance (performance value in %) per CGait subtest in the two difficulty levels of the CGait (if possible for the patients).

The CGait test measures gait adaptability using six different subtests on the CMill + VR treadmill. A comprehensive description of the CGait is provided in the publication by Timmermans et al. (2019).

During the test, the subjects are safeguarded by a harness and the comfortable walking speed is determined at the beginning of the test. This speed is maintained throughout all tasks. In the planned study project, it will also be maintained for the test with and without mask. All tasks of the CGait will be completed by the subjects first with an easy and then with a hard level of difficulty. The subjects are instructed both via an integrated screen and by the therapists.

The performance for the six test tasks (Fig. 2) "goal-directed stepping", "tandem walking", "obstacle avoidance", "slalom walking", "speed adaptations", is measured. It is determined by the proportion of steps where the center of pressure was within the projected area during the mid-stance phase (± half of the foot size for goal-directed stepping and obstacle avoidance). In the "walking with suddenly shifting obstacles and targets" task, the weighted average of correct steps and correctly avoided obstacles is calculated. For each of the six tasks a performance value between 0 and 100% is obtained.

Figure 2: Six subtests of the CGait test from Timmermans et al., 2019.

The performance values of each subtest are compared per condition (1: with facemask, 2: without facemask) and for each difficulty level (easy, hard).

#### 2.2.2 Secondary endpoints

However, since clinically observed improvement is not only a matter of standardized, objective measurements, but also of patients' self-assessment, which may also have an influence on performance, patients' subjective assessment of whether wearing a facemask has an influence on subjectively perceived walking ability is recorded by means of a survey and evaluated descriptively.

As further secondary endpoints, the central tendencies of the execution times per condition ("wearing a facemask" and "not wearing a facemask") for the respective clinical parameters (10mWT, TUG, TUG+DT and stair test) will be compared.

### 2.3 Blinding

There is no blinding of test and/or training instructors.

### 2.4 Randomization

The subjects are randomly assigned to the conditions, i.e. the order of testing (condition "with mask/without mask" or "without mask/with mask"). Both conditions should occur equally often among all participants.

### 2.5 Statistical evaluation

The collected, pseudonymized data is recorded digitally (dual control principle).

Data analysis is performed using common analysis software IBM SPSS Statistics 27.0 (Armonk, NY) and open source software R (R Foundation for Statistical Computing, Vienna).

At the beginning of the analysis, the data are checked with regard to the fulfillment of required prerequisites. The typical statistical procedures are used for the verification.

Frequencies, medians (with minimum and maximum), or means (with standard deviation) are reported to describe the sample, as appropriate.

To answer research *question 1*, whether wearing the facemask (FFP-2 mask) has an effect on the adaptability of gait (measured with the performance scores of the CGait subtests in both difficulty levels) in people with a neurological disorder, a parametric or non-parametric within-group comparison is calculated, as appropriate.

The *2nd study question*, whether wearing a facemask has an influence on the subjectively perceived walking ability of the patients, is presented using descriptive statistics (frequency tables).

In addition to these two central study questions, research *question 3* of the study, whether there is also an influence by wearing a facemask in the clinical tests measuring walking ability (10mWT, TUG, TUG+DT, and stair test), will be explored. For this purpose, parametric or non-parametric within-group comparisons will be calculated for each subtest, as appropriate.

For all within-group comparisons, the significance level is set at *p* ≤ 0.05.

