### 1.3 Questions and hypotheses:

The main question to be addressed in the planned study is whether wearing the facemask (FFP-2 mask) has an impact on the adaptability of gait (measured by the performance score (%) per CGait subtest for each of the two difficulty levels) in people with a neurological disease (*Question 1*). It is hypothesized that people with a neurological condition (Multiple Sclerosis or Parkinson's disease) will perform significantly worse on individual or all CGait subtests if they wear a facemask than if they do not (*Hypothesis 1*).

However, since clinically observed improvement cannot only be about standardized, objective measurements, the self-assessment of patients must also be given high priority. It should be clarified whether wearing a facemask has an influence on the subjectively perceived walking ability of patients (*question 2*), since it can be assumed that people with a neurological disease notice an impairment of their walking ability by wearing a facemask (*hypothesis 2*). Furthermore, it is known that the subjective perception of the patients might have an influence on gait performance (Hoogkamer et al., 2015; Rosengren et al., 1998), therefore it is relevant to ask about this.

In addition to these two main aspects of the studies, it will also be exploratively investigated whether there is also an influence of wearing a facemask in these clinical tests as well as in walking up and down stairs (*question 3*). It is possible that people with a neurological disorder also show abnormalities in common clinical tests measuring walking ability (stair test, TUG, TUG+DT, 10mWT) (*hypothesis 3*). This finding, albeit exploratory, would provide relevant information for routine clinical testing for all clinicians* who do not have CMill+VR available.

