| Fall-associated self-efficacy (Activities-Specific Balance Confidence Scale, ABC *Schott, Z Gerontol Geriat, 2008*). | Interviews | 5 min | x | x |
| Motor data (total duration 45 min., 2x each) | | | | |
| Gait adaptability (CGait, Timmermanns et al, *Phys Ther*, 2019). | Motor Test | 20 min | x | x |
| 10m walking distance (10mWT; ) | Motor Test | 5 min. | x | x |
| Functional mobility and balance (Timed Up and Go Test, TUG Mathias et al, *Arch Phys Med Rehabil*, 1986). | Motor Test | 5 min. |  | x |
| Walking with dual task (TUG with dual task, TUG+DT Hofheinz et al., *HeilberufeScience*, 2011). | Motor Test | 10 min |  | x |
| Ascending and descending stairs (acending/ decending stair test Nightingale, *J Rehabil Res Dev*, 2014). | Motor Test | 5 min. |  | x |
| Respondent interview (total duration 20 min.) | | | | |
| Subjective assessment of subjects on performance with/without mask | Survey | 15 min |  | x |
| Subjective assessment of the C-Mill by test persons | Survey | 5 min. |  | x |

*Total duration*: 150 min. of which exclusively study-related testing approx. 85 min.

*The following applies to the assessments*: If individual limitations arise due to the clinical picture or if the patients need a break for any reason, which they do not need to specify, or do not wish to continue the test/questionnaire, the test/questionnaire will be interrupted or terminated.

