### 4.3 Sample size

The planned project is to be implemented with the support of 50 test persons. This is considered a feasible sample size for the intended study period. No a priori case number calculation was performed, since no studies are available so far on the basis of which necessary à priori assumptions can be made. Due to the novelty of the topic, clinically relevant minimum differences for the intended outcome parameters have not yet been established. The planned study will make a relevant contribution to this point.

Nonetheless, a sensitivity power analysis showed that with this feasible sample size, the analysis will have a power of 0.8, will have an effect size of *d* = 0.4, and will have a power of 0.95 to identify effect sizes of *d* = 0.52 (see Fig.4)

[figure not shown]

[figure not shown]
Figure 4: Results of the sensitivity power analysis.

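### Test order is randomised but left out of the primary analysis, so any learning or fatigue effect inflates the error term and biases the mask effect if completed pairs are unbalanced

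*Protocol*

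**What the plan says.** Protocol sections 2.1 and 2.4 randomise the sequence of the two conditions and intend the two sequences to be equally frequent: "The subjects are randomly assigned to the conditions, i.e. the order of testing". Table 1 in section 2.2 lists the repeated block as "Motor data (total duration 45 min., 2x each"), of which the CGait takes 20 minutes, within a total of 150 minutes.

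Section 2.2.1 compares scores by mask condition and difficulty level only. For question 1, section 2.5 states that "a parametric or non-parametric within-group comparison is calculated, as appropriate", and then: "For all within-group comparisons, the significance level is set at *p* ≤ 0.05". The timed clinical tests get the same kind of comparison. Order, sequence and period appear in no analysis, and no check for an order effect is planned.

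Equal frequency is promised for participants, not for completed pairs. Section 2.2 allows a test to be interrupted or stopped, and section 2.2.1 makes the two difficulty levels conditional on what the patient can manage.

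**The concern.** Randomising the order stops a first-to-second-run change from systematically favouring one condition. It does not remove that change from the data. In a plain paired comparison, participants who wore the mask second have the period effect added to their difference, and those who wore it first have it subtracted. This extra spread is counted as random error although it is fully explained by a known, randomised factor.

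A period effect is plausible here. The same 20-minute treadmill test is repeated at the same fixed speed, inside a long session, in patients whose physical and mental capacity may be limited according to the section on complications and risks. Repetition could improve the second run, and fatigue could worsen it.

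Two things are at stake. With equal orders, power is lost in a trial whose size is set by feasibility at 50. With unequal completed pairs, the period effect no longer cancels and part of it is reported as a mask effect. Pairs can be lost separately in each of the 12 primary comparisons (six subtests at two levels).

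**Working it through.** **Inputs from the protocol.** n = 50 (section 4.3), significance level 0.05 per comparison (section 2.5), two orders in equal numbers, so 25/25 (sections 2.1 and 2.4). Sidedness is not stated.

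**Inputs assumed.** The protocol gives no period effect, no SD of differences and no rate of incomplete pairs. Period effects (second minus first run) of 0 to 1 SD of the within-person difference and several splits of completed pairs are used below.

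**Step 1: the plan's own figures.** Section 4.3 says "the analysis will have a power of 0.8, will have an effect size of *d* = 0.4". Its second figure pairs d = 0.52 with 95% power. A two-sided paired t-test with n = 50 and 49 degrees of freedom (noncentral t) gives power 0.792 at d = 0.4 and 0.950 at d = 0.52. Exactly 80% needs d = 0.404. One-sided testing gives 0.874 and 0.976, which does not match. The power statement is therefore that of a plain two-sided paired t-test with no order term.

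**Step 2: the model.** Let D be the mask minus no-mask difference, τ the mask effect, π the period effect and e an error with SD 1. Then D = τ + sπ + e, with s = +1 if the mask came second and s = −1 if it came first.

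**Step 3: balanced orders (25/25).** The mean of D is unbiased for τ. Its variance, ignoring order, is 1 + π², and the expected sample SD rises by about √(1 + π²·50/49). At π = 0.5 this is √1.255 = 1.12; at π = 1 it is √2.020 = 1.42. The effect detectable with 80% power rises by the same factor: 0.404 × 1.12 = 0.453 and 0.404 × 1.42 = 0.575 (unrounded factors). Simulation with 100,000 trials per setting and true |τ| = 0.404 gives:

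| Period effect (SD) | Power, paired t | Power, order-adjusted | Type I error, paired t |
|---|---|---|---|
| 0 | 0.80 | 0.80 | 5.0% |
| 0.2 | 0.79 | 0.80 | 4.6% |
| 0.3 | 0.78 | 0.80 | 4.0% |
| 0.5 | 0.73 | 0.80 | 2.9% |
| 0.8 | 0.61 | 0.80 | 1.3% |
| 1.0 | 0.50 | 0.80 | 0.6% |

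The adjusted analysis averages the two order-specific means, uses the pooled SD and has 48 degrees of freedom. Its type I error stays at 5%.

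**Step 4: unbalanced completed pairs.** The bias of the unadjusted mean is π(n_mask second − n_mask first)/n. With 24 mask-first and 18 mask-second pairs it is π(18 − 24)/42 = −0.143π. At a period effect of 0.5 SD the bias is 0.071 SD in size. If it works against the mask effect, paired-test power is 0.47, against 0.72 adjusted; if it works with the effect, paired-test power is 0.79. Type I error of the paired test at 24/18 does not exceed 5%. At 25/15 the bias is 10/40 = 25% of the period effect, and type I error rises to 8.0% at 0.5 SD and 11.7% at 1 SD, while the adjusted test stays at 5%.

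**Step 5: cost of adjusting when it is not needed.** With no period effect, power is 0.80 for both methods at 25/25, and 0.73 (paired) against 0.72 (adjusted) at 24/18.

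**The case against.** The strongest reply is that the design already handles order. With equal orders the paired test is unbiased and conservative, so the issue is efficiency and not validity. That stands for balanced pairs.

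The size of the harm is also uncertain. Period effects of 0.5 and 1 SD are assumptions. At 0.2 to 0.3 SD with balance, the loss is one to two percentage points of power. Learning and fatigue may offset each other, some patients may already know the CGait because Table 1 marks it as routine, and breaks are allowed. Incomplete pairs need not be unequal between orders: a patient who cannot do the hard level may well lack it in either order, and if loss is unrelated to order the bias is zero on average. At 24/18 there is no inflation of type I error. These are real limits on the expected harm.

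The last argument is that a model with a period term could itself be called a parametric within-participant comparison, and that such terms are often left to an SAP. This is weaker. Sections 2.2.1 and 2.5 state the comparison by condition alone, and the power figures in section 4.3 are those of a plain paired t-test. The protocol thus describes an analysis that drops a factor it randomises. If an SAP adds the term, section 2.5 should say so too.

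**Conclusion.** The concern holds. The planned primary comparison ignores the randomised order. With 25/25 completed pairs the consequence is lost power and a conservative test: negligible for a period effect up to about 0.3 SD, 0.73 instead of 0.80 at 0.5 SD, and 0.50 instead of 0.80 at 1 SD. With unequal completed pairs the estimate is also biased, by 14% of the period effect at 24/18 and 25% at 25/15. Material inflation of type I error needs a strong imbalance together with a moderate or large period effect.

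The results assume normally distributed differences and the same period effect in both orders. The algebra is certain; the practical size depends on a period effect that the protocol does not give. This should be changed before data collection. The sample size is fixed by feasibility, so lost power cannot be regained by recruitment, and section 2.6 plans a Registered Report in which the approved method has to be followed.

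**What to change.** In section 2.5, specify the analysis of each CGait outcome, and of each timed clinical test, as a two-period crossover by one of two routes:

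- A linear mixed model with condition and period as fixed effects and participant as a random effect.
- A comparison of the first-minus-second-run differences between the two orders, by t-test, or by rank-sum test with a Hodges–Lehmann estimate where scores are bounded or tied. Half the between-order difference estimates the mask effect.

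Name one method in advance and use it for all 12 primary outcomes. Report the estimated period effect, and the number of completed pairs by order for each outcome.

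The cost is a few sentences in section 2.5, one model term and one degree of freedom. No new measurement is needed. The data items listed in sections 2.1 and 2.2 do not name the order of testing, so the case report form should include the order actually followed.

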### 2.2 Assessments

The data to be collected will be obtained by interview (sociodemographic and clinical data and subjective assessments) and simple clinical examination (motor gait and balance tests). Table 1 summarizes the assessments planned for the study. Most of the data to be collected in the project will be collected in the usual routine. Therefore, the additional burden for the subjects is low (85 min.).

The sociodemographic and clinical data can largely be taken from the digital file. However, they are verified in personal interviews with the patients and the treating physicians (questioning).

The recording of past fall events and fall-associated self-efficacy is carried out by means of standardized questionnaires. The self-evaluation of the test persons is carried out with self-developed questionnaires.

During motor testing, various facets of mobility are recorded using standardized assessments for neurological rehabilitation. The testing is performed by experienced physiotherapists and/or sports scientists who have been familiar with the testing for many years. The assessments cannot be blinded due to staff resources.

Table 1: Planned assessments

| **Tests** | **Form of collection** | **Duration** | **Routine** | **T0** |
| --- | --- | --- | --- | --- |
| Sociodemographic data (total duration approx. 7 min.) | | | | |
| Age in years | File/ Questioning | < 1min. | x | x |
| Gender | File/ Questioning | < 1min. | x | x |
| Training years | File/ Questioning | < 1min. | x | x |
| Weight in Kg | File/ Questioning | < 1min. | x | x |
| Body height in cm | File/ Questioning | < 1min. | x | x |
| Body Measure Index, BMI | Is calculated from height and weight (formula of WHO )^[[1]](#footnote-1)^ |  |  |  |
| Shoe size | Survey | < 1min. |  | x |
| Spectacle wearer | Survey | < 1min. |  | x |
| Type of visual impairment | Survey | < 1min. |  | x |
| Clinical data (total duration approx. 13 min.) | | | | |
| Diagnosis incl. progression form/ type | File/ Questioning | < 1min. | x | x |
| Time since diagnosis (in months) | File/ Questioning | < 1min. | x | x |
| Severity of illness (Expanded Disability Status Scale, EDSS Kurtzke, *Neurol,* 1983; Hoehn & Yahr Scale.  Hoehn & Yahr, Neurol, 1967) | File/survey for motor. Testing | 5 min. | x | x |
| Fall events in the last 12 months | Survey | < 1min. |  | x |

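### Question 2 is called central and has its own hypothesis, but frequency tables without an interval or criterion leave a middling result at n = 50 unreadable

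*Protocol*

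**What the plan says.** **Rank of the question.** Protocol section 1.3 states that "the self-assessment of patients must also be given high priority". It gives Question 2 its own Hypothesis 2, that "it can be assumed that people with a neurological disease notice an impairment of their walking ability by wearing a facemask". It then introduces the exploratory Question 3 with "In addition to these two main aspects of the studies", and section 2.5 repeats this ranking with "In addition to these two central study questions".

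**Planned analysis.** Section 2.5 asks whether the mask influences perceived walking ability and says that this "is presented using descriptive statistics (frequency tables". Section 2.2.2 places the same assessment among the secondary endpoints and says that it "is recorded by means of a survey and evaluated descriptively". No interval, test or benchmark for Hypothesis 2 appears in the protocol.

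**Contrast.** Section 2.5 gives the exploratory Question 3 (10mWT, TUG, TUG+DT, stair test) within-group comparisons for each test at p ≤ 0.05.

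**Instrument.** Section 2.2: "The self-evaluation of the test persons is carried out with self-developed questionnaires". Table 1 lists a 15-minute survey on performance with and without the mask. The items and the response scale are not given.

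**The concern.** Question 2 is phrased as a whether-question and carries a directional hypothesis, but the stated analysis has no means of saying how precise the answer is. A frequency table gives a count and a percentage. With 50 patients the sampling error of a percentage is about 10 to 15 points either way, so the same table is compatible with quite different conclusions when the split is moderate.

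What is at stake is the conclusion on a question that the protocol ranks beside the primary one. If it is not fixed beforehand what would count as support for Hypothesis 2, that judgement is made after the counts are seen. The primary endpoint (the CGait performance values) is not affected.

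**Working it through.** **1. The plan's own figures.** Section 4.3 gives N = 50, power 0.8 at d = 0.4 and power 0.95 at d = 0.52. For a two-sided paired t-test with df = 49, α = 0.05 and noncentrality d·√50:

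- d = 0.40: power 0.792; the d for power 0.80 is 0.404.
- d = 0.52: power 0.950; the d for power 0.95 is 0.520.

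The figures reproduce. They concern within-group comparisons of a continuous score and say nothing about Question 2, for which the protocol has no figure.

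**2. Inputs for Question 2.** n = 50 is from section 4.3. The rest is assumed because the questionnaire is not shown: a single item answered worse or better with the mask, no ties, and a benchmark of 50% (an even split). Hypothesis 2 itself names no proportion.

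**3. Precision of a proportion.** The exact (Clopper-Pearson) 95% limits for x of n are the 0.025 quantile of Beta(x, n − x + 1) and the 0.975 quantile of Beta(x + 1, n − x). The exact two-sided sign test for x > n/2 is p = 2·P(X ≥ x) with X ~ Bin(n, 0.5).

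| Worse with mask | Share | Exact 95% CI | Sign test p |
| --- | --- | --- | --- |
| 5/50 | 10% | 3% to 22% | (clearly below half) |
| 25/50 | 50% | 36% to 64% | (even split) |
| 30/50 | 60% | 45% to 74% | 0.20 |
| 32/50 | 64% | 49% to 77% | 0.065 |
| 33/50 | 66% | 51% to 79% | 0.033 |
| 40/50 | 80% | 66% to 90% | < 0.001 |

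The extreme rows can be read without help. The rows from 50% to 64% are all compatible with an even split, and a bare percentage does not show it.

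**4. Power of the illustrative test.** With at least 33/50 required, the chance of reaching it is 0.24, 0.51, 0.78 and 0.94 when the true share is 60%, 65%, 70% and 75%. The sample can therefore inform Question 2 if the effect is marked.

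**5. Effect of ties.** The sign test uses only the patients who answer worse or better. Applying the same formula to fewer informative answers (numbers of ties assumed):

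- 10 ties, 40 informative: 27 worse needed (2·P(X ≥ 27) = 0.038; 26 gives 0.081).
- 20 ties, 30 informative: 21 worse needed (2·P(X ≥ 21) = 0.043; 20 gives 0.099).

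In the first case 27/50 = 54% report worse walking (exact 95% CI 39% to 68%), although the sign test is below 0.05. Once a same answer is possible, the interval describes how many notice an impairment and the test describes direction among those who notice a change. Both are needed, and 33/50 is not a general threshold.

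**The case against.** The strongest reply is that description is a deliberate and consistent choice. Sections 2.2.2 and 2.5 agree, the item is listed as secondary, and central or high priority expresses importance without promising a confirmatory test. Hypothesis 1 speaks of significantly worse performance; Hypothesis 2 says only that patients "notice an impairment of their walking ability by wearing a facemask". The instrument is self-developed and its format unseen, so neither the pairing of answers nor the 50% benchmark can be taken from the document. Patients know whether they wear a mask, so a p-value would not remove expectation bias. An interval could also be added in a statistical analysis plan.

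Most of this stands as a limit on the point. A reader might infer that Hypothesis 2 can be neither supported nor refuted as planned. The protocol does not bear that out: 5/50 and 40/50 would read very differently in a plain table. Nor does the protocol say that any majority would be taken as confirmation, and a reader with the counts could compute an interval.

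Two things remain. First, the protocol does not leave the method open: it specifies frequency tables for a question it ranks as central, and tests the question it ranks as exploratory. Second, section 2.6 plans a Registered Report, in which the method is reviewed before data collection, so a criterion for a numbered hypothesis fits in this text. Reporting an interval survives every objection above; the sign test depends on a suitable item existing.

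**Conclusion.** The point holds in a limited form. The rank given to Question 2 and its planned analysis do not match: there is a numbered hypothesis and no interval or criterion by which to judge it. The consequence is confined to middling results. Under the illustrative assumptions (worse/better item, no ties, 50% benchmark, n = 50), shares up to 32/50 (64%) have an exact 95% CI that reaches an even split, and 33/50 (66%) is the first that does not; ties change that boundary. Clear results remain readable descriptively. A purely descriptive analysis is legitimate if the question is labelled so. The change is worth making because it costs little, but it does not touch the primary comparison.

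**What to change.** In section 2.5:

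1. Name one overall-walking item from the self-developed questionnaire and classify each participant as worse, same or better with the mask.
2. Report the share worse with the mask, of all who answered, with an exact 95% CI.
3. As a secondary analysis, give an exact sign test of worse versus better, stating the number of ties. If each condition is rated separately on a graded scale, use the Wilcoxon signed-rank test on the paired ratings.
4. Keep the remaining items descriptive.

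Do not make this analysis conditional on a global test of Question 1: section 2.5 plans none, and perceived and measured effects may differ.

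If the questionnaire contains no such item, relabel Hypothesis 2 as a descriptive expectation and report the proportions with 95% CIs.

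**Cost.** A few sentences and one more secondary analysis; no extra patients or visits. The questionnaire must contain the named item. The result stays open to expectation bias because patients know whether they wear a mask, and the report should say so.
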